### Adverse events:

The study investigators will oversee and monitor all aspects of the study including subject consent, study conduct, data handling as well as reporting any adverse events to the local ethical committee and Swissmedic

### Assessment of Risk:

The procedures included in this study are considered to present only mild risk to research participants. However, the study will be reviewed and reported as required by the “Verordnung über klinische Versuche mit Heilmitteln des Schweizerischen Bundesrates vom 17. Oktober 2001”.

### Attribution of Adverse Events:

Adverse events will be monitored for every subject participating in the study and attributed to the study procedures/design by the study investigators according to the following categories:

Possible: Adverse event(s) may be related to investigational procedure(s)/agent(s) or other intervention.

Unlikely: Adverse event(s) will doubtfully be related to investigational procedure(s)/agent(s) or other intervention.

### Plan for Grading Adverse Events:

The following grade levels will be used in defining the severity of adverse events:

Serious: Death, immediate risk of death, hospitalization or a prolongation of existing hospitalization or a persistent or significant disability/incapacity.

Non-serious: Mild or moderate adverse event or within normal limits.

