The subjects’ consciousness during the insulin infusion study will be rated using the Glasgow coma scale (GCS) rating system every 5 min after plasma glucose has dropped below 3.5 mmol/l. If the grading decreases below 3 for best eye response (eye opening to speech), 3 for best verbal response (inappropriate words), 4 for best motor response (withdraws from pain) or plasma glucose concentrations decrease below 1.5 mmol/l, the insulin infusion will be stopped or tapered and small amounts of glucose (5-10g or 25-50 ml of a 20% dextrose infusion) will be given intravenously until the GCS rating and plasma glucose have increased above the previously mentioned limits.

Due to the prolonged duration of action of glibenclamide and its potential glucose lowering effects in type 1 diabetics with residual -cell function, patients will be instructed to taper their usual insulin dose **by 30 %** and monitor their capillary blood glucose every two to four hours and any time after the onset of symptoms suggestive of hypoglycemia for 24 hours after oral application of glibenclamide. They will be asked to ingest 10 grams of oral dextrose if capillary blood glucose concentrations drop below 4.0 mmol/l. When ever correction of blood glucose levels < 4.0 mmol/l becomes necessary, a repeat glucose measurement will be performed after one hour. All participants will be provided with the phone number of a study investigator in case any problems should arise after discharge from the clinical research center. **All patients will be advised to refrain from vigorous physical activity and driving motor vehicles within 24 hours after the ingestion of the study drugs**. **Furthermore, patients will be advised to increase the dosage of short acting insulin if blood glucose readings exceed 10 mmol/l.**

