### Plan for reporting serious adverse events:

While no serious adverse events are expected, the study investigators will report any serious adverse events to the local ethical committee and Swissmedic within 48 hours.

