### Plan for reporting non-serious adverse events:

Non-serious unanticipated adverse events will be reported to the local ethical committee on an annual basis.

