## Time schedule:

Start of the study: March 2007

Duration: 9 months including recruitment period.

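### The adverse event scale merges severity with seriousness, so a severe event that is not serious is graded mild or moderate, and the annual non-serious report, counted from study start, falls due after the 9-month study ends

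*Protocol*

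**What the plan says.** All references are to the Protocol.

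- **Plan for Grading Adverse Events** introduces its scale with "The following grade levels will be used in defining the severity of adverse events". It then gives two levels: "Serious: Death, immediate risk of death, hospitalization or a prolongation of existing hospitalization or a persistent or significant disability/incapacity" and "Non-serious: Mild or moderate adverse event or within normal limits".
- **Plan for reporting serious adverse events** sets the fast route: "the study investigators will report any serious adverse events to the local ethical committee and Swissmedic within 48 hours".
- **Plan for reporting non-serious adverse events** sets the slow one: "Non-serious unanticipated adverse events will be reported to the local ethical committee on an annual basis".
- **Time schedule** gives "Start of the study: March 2007" and "Duration: 9 months including recruitment period".
- **Adverse events** (the short general section) has the investigators report any adverse event to the ethics committee and to Swissmedic, with no time limit.
- **Data and safety review and frequency** has the investigators themselves review data and conduct every week.
- **Safety measures**, under Intravenous insulin infusion study 1, foresees impaired consciousness and very low glucose. The trigger begins "If the grading decreases below 3 for best eye response (eye opening to speech), 3 for best verbal response (inappropriate words" and goes on to motor response and a plasma glucose below 1.5 mmol/l. The response is to stop or taper the infusion and give intravenous glucose. **Potential risks** repeats that both events are foreseen and expects a nadir of around 2.0 mmol/l.

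**The concern.** Severity describes how intense an event is. Seriousness describes its outcome or the danger it poses. The scale says it grades severity, but it defines its upper level by outcome and its lower level by intensity. An event that is severe in intensity and meets none of the outcomes fits neither wording. Since it is not Serious, it ends up in the level described as mild or moderate.

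The gap falls on the event this trial is most likely to produce. Hypoglycaemia is induced on purpose, twice per patient, so 20 x 2 = 40 infusion visits are planned. The patient is already an inpatient for about 22 hours. An episode of impaired consciousness that is reversed with intravenous glucose need not prolong the stay or leave disability. The protocol uses the missing category elsewhere: under Study population, a severe hypoglycaemia in the past four weeks bars entry, yet the same event during the trial has no severe grade.

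The grade also decides the reporting route. A serious event goes to two outside bodies within 48 hours. A non-serious one goes to one body, once a year, and only if it was not anticipated. The risk is that safety tables understate how severe the induced episodes were, and that the ethics committee receives no scheduled account of them while patients are still being studied.

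**Working it through.** No sample size, power or error rate enters this point. The check sets the sections side by side and adds calendar arithmetic.

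**Step 1: where does a severe episode reversed on site fall?** Take impaired consciousness during the infusion, treated under Safety measures, with full recovery and discharge at the planned 5:30 p.m.

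| Criterion for Serious | Met? |
|---|---|
| Death | No |
| Immediate risk of death | Only if the investigator judges it so |
| Hospitalization or its prolongation | No: already admitted, discharged on time |
| Persistent or significant disability | No |

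Unless that one judgement is made, the event is non-serious, and the scale describes it as mild or moderate.

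**Step 2: does the non-serious reporting rule cover it?** That rule is limited to unanticipated events. Safety measures and Potential risks both foresee impaired consciousness, so it can be read as anticipated and left out of the annual report. A seizure is different. Neither section lists it as an expected event; it appears only as a history that excludes patients. It would be unanticipated and so covered.

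**Step 3: when does an annual report fall due?** Inputs: start in March 2007, duration 9 months, reporting interval 12 months.

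- Planned end: a start on 1 March gives about 30 November 2007, and a start on 31 March gives about 31 December 2007.
- Counted from study start: the first report is due in March 2008, which is 12 - 9 = 3 months after the end.
- Counted by calendar year: due on or after 31 December 2007, at or after the end.
- Counted from an approval date *a* months before the start: due at month 12 - *a*. This is inside the study only if 12 - *a* < 9, that is *a* > 3. The protocol gives no approval date.

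**Step 4: do the two reporting statements agree?**

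| | Adverse events | Plan for reporting non-serious adverse events |
|---|---|---|
| Scope | Any event | Non-serious and unanticipated |
| Recipient | Ethics committee and Swissmedic | Ethics committee |
| Time | None given | Annual |

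They differ in scope and in recipient, and only the narrower one gives a time.

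**The case against.** The strongest reply is that a reader might infer from the grading and reporting rules that the trial's main hazard could be reported to nobody outside the team. The protocol does not support that. The general Adverse events section sets a duty to report any event to both outside bodies, and the annual rule does not cancel it. Assessment of Risk adds that the study will be reported as the Swiss ordinance requires. The ordinance is not at hand, so its absence from this account proves nothing either way. This part of the reply stands. What remains is that the general duty has no time attached and disagrees with the specific rule.

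A second reply is that the grade hides little. Glucose is measured every 5 to 10 minutes, consciousness is rated every 5 minutes below 3.5 mmol/l, and the investigators review the data weekly. This is also right: the raw records survive. But the weekly review is internal, and a source record does not correct a grade.

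A third reply is that Serious reaches further than it seems. The Introduction says hypoglycaemia can be fatal, so coma or a seizure may well be judged an immediate risk of death, and keeping a patient past the planned discharge would count as prolonged hospitalization. This narrows the gap to episodes that are fully reversed on site and not judged life-threatening, but does not close it.

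A reader might also infer that the trial would end by declaring its procedures only mildly risky because the scale allows nothing else. That is speculation. The statement about mild risk in Assessment of Risk is made in advance, about the procedures, and is not an output of the scale.

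**Conclusion.** Wrong as written, minor. Three defects are on the page:

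1. The scale has no level for a severe event that is not serious, and by exclusion it labels such an event mild or moderate.
2. Counted from study start, no annual non-serious report falls due while patients are being studied; the first comes 3 months after the planned end. This assumes the stated 9-month duration is kept and that the interval does not run from an approval date more than 3 months before the start.
3. The general and the specific reporting statements conflict on scope and recipient.

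The 40 planned infusion visits measure exposure. They are not a count of misgraded or unreported events, and the protocol gives no basis for estimating one. The primary endpoint and its analysis are untouched.

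**What to change.** - In Plan for Grading Adverse Events, grade severity (mild, moderate, severe) separately from seriousness, and keep the existing outcome list for seriousness.
- State how an episode that triggers the existing Safety measures, and any seizure, is recorded and to whom and when it is reported, even if it was anticipated. This need not mean that every glucose value below 1.5 mmol/l is classed as severe and sent within 48 hours, since the planned nadir is already around 2.0 mmol/l and such a value may come without symptoms.
- Reconcile Adverse events with Plan for reporting non-serious adverse events, so that scope and recipient agree.
- Replace the annual interval with one report that falls within the 9 months and one at the end.

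The cost is protocol wording, one field on the case report form and an extra summary report. The change concerns recording and reporting only; no dose, threshold or treatment rule changes.

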### Plan for reporting serious adverse events:

While no serious adverse events are expected, the study investigators will report any serious adverse events to the local ethical committee and Swissmedic within 48 hours.

### Plan for reporting non-serious adverse events:

Non-serious unanticipated adverse events will be reported to the local ethical committee on an annual basis.

### Data and safety review and frequency:

The study investigators will review the data and study conduction on a weekly basis and determine whether the study should continue unchanged or whether modifications to the protocol and/or consent form are required.

## Statistical Considerations:

### Data analysis:

The primary endpoint for the comparison of patients with diabetes type 1 with and without treatment with glibenclamide will be the area under the curve of plasma glucagon concentrations from time 0 (start of the insulin infusion) to time 150 (150 min after the onset of the insulin infusion).

The secondary endpoint will be the rate of recovery of plasma glucose concentrations from 60 to 150 min, after tapering the insulin infusion to 15 mU/m2/min.

Further secondary endpoints will be the relation of symptoms and signs of hypoglycemia and hypoglycemia awareness to counter-regulatory hormone concentrations during insulin induced hypoglycemia.

The data analysis consists of the analysis of the primary and secondary endpoint. Data will be expressed as means ± SEM, Analysis of variance and appropriate post hoc analysis will be used to assess the effect of glibenclamide therapy over time. Unpaired t-tests and Mann-Withney U-tests will be used to compare baseline parameters between groups.

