# Study objectives:

To demonstrate that oral administration of glibenclamide stimulates pancreatic glucagon secretion during hypoglycemia in insulin-deficient (C-peptide negative) patients with type 1 diabetes when compared to type 1 diabetic patients with residual insulin secretion (C-peptide positive).

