# Study design and methods:

## General description of the study:

Patients with type 1 diabetes participating in this single-blind, randomized cross-over study evaluating the effect of glibenclamide on glucagon secretion during insulin induced hypoglycemia. Glucose and glucagon metabolism will be studied using an intravenous insulin infusion test. We anticipate that patients diagnosed with C-peptide negative type 1 diabetes will increase glucagon secretion after oral administration of glibenclamide compared to patients with type 1 diabetes with maintained residual -cell function.

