A web-based random number generator ([www.random.org](http://www.random.org/)) will be used to assign a random number between 1 and 10 to each patient at the beginning of the first insulin infusion study. Those assigned an even number will receive glibenclamide during the first insulin infusion study and placebo pills during the second study. Patients assigned an odd number will receive the 2 therapies in reverse order.

*Insulin infusion and blood sampling:*

The intravenous insulin infusion test will be started at 8:30 a.m.. Regular human insulin will be infused at the rate of 30 mU/m²/min for 60 min and 15 mU/m²/min thereafter from 60 to 150 min in type 1 diabetics with a syringe pump (Braun perfusor® compact S) as previously described (19).. Venous blood samples will be taken at -30, -15, 0 min and at 5-10-min intervals over the next 150 min for the measurement of plasma glucose and at 15 min intervals for the measurement of plasma glucagon, epinephrine, metanephrine, growth hormone and cortisol concentrations. At the completion of the intravenous insulin study, the insulin infusion will be stopped, and 20% dextrose solution will be infused to re-establish normal glucose levels (4-8 mmol/l). The glucose infusion will be stopped when plasma glucose has stabilized >5 mmol/l for 30 min and a lunch will be served along with s.c. short acting insulin as needed. A total of 150 ml blood will be drawn during a metabolic stud

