### Sample size calculation:

The sample size calculation for patients with C-peptide negative diabetes type 1 is based on ANCOVA comparing glucagon levels and an expected increase of 30% after glibenclamide treatment and =0.05 using the following formula:

2[Z+Z]2 [s] 2

= N

2

where N is the required sample size, Z and Z are the false positive and false negative error rates tolerates (Z =1.96 (95%, 2 tailed); Z=0.84 (80% 1-tailed), s2 is the variance based on prior studies (square of the standard deviation (SD)) and  is the difference in the primary endpoint (change glucagon levels). The Glucagon level was found to be 22 ± 3 ng/l in patients with diabetes type 1 (13). The sample size will be 8. 10 patients per group will be recruited in order to account for potential drop-outs.

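### The protocol names two different analyses, an ANOVA over time and an ANCOVA, and ties neither to the glucagon AUC, the cross-over or the C-peptide contrast

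*Protocol*

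**What the plan says.** The Data analysis section defines the primary endpoint as "the area under the curve of plasma glucagon concentrations from time 0 (start of the insulin infusion) to time 150" min. For the treatment effect it gives one method: "Analysis of variance and appropriate post hoc analysis will be used to assess the effect of glibenclamide therapy over time". It does not name the post hoc procedure. It mentions unpaired tests only for comparing baseline parameters between groups.

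The Sample size calculation section says that the calculation for C-peptide negative patients "is based on ANCOVA comparing glucagon levels". It names no covariate, uses the formula for two independent groups, and describes the quantity to be detected as "the difference in the primary endpoint (change glucagon levels").

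The General description calls the trial a "single-blind, randomized cross-over study evaluating the effect of glibenclamide on glucagon secretion during insulin induced hypoglycemia". Sequence is set by an even or odd random number per patient. The Study objectives ask for an effect in C-peptide negative patients "when compared to type 1 diabetic patients with residual insulin secretion (C-peptide positive").

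Under Intravenous insulin infusion study 1, the study drug is given at 7:30 a.m. and the insulin test starts at 8:30 a.m. "Venous blood samples will be taken at -30, -15, 0 min", and then through the test, with glucagon every 15 min. A further baseline sample is taken at admission the evening before. Its analytes are not stated.

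**The concern.** An AUC has no time dimension left, so an analysis of the effect over time with post hoc tests is not, as worded, a test of the primary endpoint. It leaves open whether the AUC, a treatment-by-time term or a selected time point decides the trial. The sample size section then names a different method and describes the endpoint as a change in levels.

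Neither sentence reflects that each patient is their own control, that there are two periods, or that the objective is a comparison of the drug effect between two C-peptide groups. At stake are the precision of the treatment estimate, its freedom from period effects, and whether the result answers the stated objective.

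The choice of baseline raises a further problem. An ANCOVA needs a covariate, and the samples nearest the test are all taken after the drug. With no baseline at all, the AUC cannot show whether glibenclamide restored a response to hypoglycemia, which is the hypothesis in the Introduction, or simply raised glucagon throughout.

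**Working it through.** **1. The plan's own figure.** Inputs from the Sample size calculation: 1.96, 0.84, s = 3 ng/l, and a difference of 30% of 22 = 6.6 ng/l. The formula gives 2 × (1.96 + 0.84)² × 3² / 6.6² = 141.12 / 43.56 = 3.24, so 4 per arm. The stated 8 is not reproduced; it matches 2 × 4 as a total over two arms. That is a separate matter and does not decide this point. What matters here is that the formula has no within-patient correlation, so the sizing does not describe the cross-over. Its inputs are also concentrations, not AUCs.

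**2. Pairing.** Let σ be the between-patient SD of the AUC, ρ the within-patient correlation (not given; 0.5 and 0.8 assumed) and n the number of patients.
- Paired variance of the treatment difference: 2σ²(1 − ρ)/n.
- Variance if pairing is ignored: 2σ²/n.
- Ratio of standard errors: 1/√(1 − ρ) = 1.41 at ρ = 0.5 and 2.24 at ρ = 0.8.

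A simulation (40,000 runs, 10 patients, effect of 1 SD, two-sided 5%) gives power of 58% unpaired against 80% paired at ρ = 0.5, and 62% against 99% at ρ = 0.8.

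**3. Period.** Each patient is taken to get an even or odd number with probability 1/2, independently, since no blocking is stated.
- P(7:3 or worse in 10) = 2 × (1 + 10 + 45 + 120)/1024 = 352/1024 = 34%.
- P(8:2 or worse) = 2 × (1 + 10 + 45)/1024 = 112/1024 = 11%.
- With a 7:3 split and no period term, the mean within-patient difference carries (7 − 3)/10 = 40% of any period effect. With 8:2 it carries 60%.

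**4. Baseline timing.** Time 0 is 8:30, so −30, −15 and 0 min are 8:00, 8:15 and 8:30, which is 30, 45 and 60 min after the 7:30 dose. The evening sample, at admission between 8 and 9 p.m., is 10.5 to 11.5 h before the dose and precedes the overnight glucose stabilisation.

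**5. Adjusting for a post-dose baseline.** Let b be the covariate slope and f the share of the drug effect already present in the baseline sample (both assumed). The adjusted effect is (1 − b × f) of the true one.
- b = 0.5, f = 0.5: 75% retained.
- b = 0.3, f = 0.25: 93% retained.
- b = 0.8, f = 1: 20% retained.

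The protocol expects the drug's plasma peak about 2 h after ingestion (9:30), so f may well be below 1 at 8:00 to 8:30.

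**6. What the raw AUC can show.** For illustration, take a constant 22 ng/l on placebo and a constant 30% rise, 28.6 ng/l, on glibenclamide.
- Placebo AUC: 22 × 150 = 3300 ng·min/l.
- Glibenclamide AUC: 28.6 × 150 = 4290 ng·min/l.

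This is the whole target effect with no response to hypoglycemia on either day. The incremental AUC above the 0 min value is 0 on both days.

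**The case against.** Analysis of variance is a family that includes repeated-measures and cross-over models. The protocol reserves unpaired tests for baseline comparisons, and model terms are commonly left to a SAP, which is not at hand. A reader might infer that the planned ANOVA omits the patient term; the text does not say so, and the figures in steps 2 and 3 apply only if these terms are in fact left out. The 34% also needs independent draws: if numbers were issued without repeats within each group of 10, the split would be 5:5 before drop-outs.

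A reader might also infer that a baseline-adjusted result is planned and biased toward no effect. No covariate is named, the AUC is defined without subtraction, and the change in levels can be read as the treatment difference. Nor are post-dose samples the only baselines, since the evening sample exists.

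It is tempting as well to predict a large false-positive rate from treating time points as replicates or from uncorrected post hoc tests. The text describes neither practice, so no such figure is supported.

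Finally, the objective speaks of stimulating secretion during hypoglycemia, which the raw AUC does measure. That is fair, and it is why the AUC should stay primary. The hypothesis in the Introduction, however, is that the defective response is restored, and the same section cites a glucagon rise after oral glibenclamide, so a tonic rise is a live alternative.

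What the objection does not remove is that two sections name different methods and neither is attached to the endpoint, the design or the group contrast.

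**Conclusion.** The point holds as a conflict and a missing link within the protocol, not as proof of a wrong model. The documents establish that ANOVA over time and ANCOVA are both named, that neither is tied to the AUC, the cross-over or the C-peptide contrast, and that every baseline sample timed to the test is post-dose.

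The sizes are conditional. The standard error inflation of 1.41 to 2.24 rests on assumed correlations and on pairing being ignored. The 40% share of a period effect needs a 7:3 split and no period term. The loss from baseline adjustment depends on an assumed slope and on how early the drug acts. The 3300 to 4290 ng·min/l example assumes a flat profile. The matter should be corrected, and correction is cheap. The model can be settled in wording, but the lack of a pre-dose glucagon sample near the test cannot be repaired once the visits are done.

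**What to change.** 1. Name one primary analysis, in the same words, in the Data analysis and Sample size calculation sections: glucagon AUC 0–150 per visit in a linear mixed model with treatment, period, C-peptide group and treatment-by-group as fixed effects and patient as random effect. Report within-patient differences with 95% confidence intervals, and the treatment-by-group contrast that the objective calls for. Keep time-point comparisons descriptive.
2. Draw one glucagon sample before the 7:30 dose from the line already in place. If a baseline covariate is used, use only that one.
3. Add the incremental AUC above the 0 min value as a secondary endpoint. Interpret it as the hypoglycemia-driven component only, not as the total drug effect, because subtracting a post-dose value removes any effect already present by then. A tonic effect that is still building after time 0 would remain in it, so it should be read beside the raw AUC.

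Cost: protocol wording and one extra tube per visit, with the stated blood volumes checked accordingly. The incremental AUC is noisier than the raw AUC, which is a reason to keep it secondary.
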